**Figure 1 F1:**
[figure not shown]
Hemodynamic algorithm based on pCO_2_ gap/P(a–v)O_2_ ratio. RBC, red blood cell; SvO_2_, mixed venous oxygen saturation; PEEP, positive end-expiratory pressure; FiO_2_, fraction of inspired oxygen.

**Figure 2 F2:**
[figure not shown]
Usual hemodynamic algorithm. MAP, mean arterial pressure; PEEP, positive end-expiratory pressure; FiO_2_, fraction of inspired oxygen; RBC, red blood cell.

### Randomization

The 1:1 ratio randomization (stratified on center and type of shock) is performed by the investigator after the patient's enrollment, using a dedicated e-platform made with CleanWebTM. The security of this process is assured by individual usernames and newly created passwords for each enrolment. A second check for the inclusion, non-inclusion, and exclusion criteria is required before continuing with the randomization. Technical support is provided by the Research Methodology Support Unit from our university-affiliated hospital, which also keeps a record of the full randomization process. Statistical analysis is performed by a statistician of the Research Methodology Support Unit who is not involved in the study process.

### Objectives

The primary objective is to compare hyperlactatemia treatment effectiveness between an algorithm based on CO_2_-O_2_-derived indices and usual clinical practice after 2 h (3, 20).

The secondary objectives are as follows: (1) to compare lactate clearance at H12 and H24 between the two strategies; (2) to compare the number of patients with blood lactate levels <2 mmol l^−1^ at H12, H24, and H48; (3) to evaluate the ability of P(v–a)CO_2_/C(a–v)O_2_ to predict blood lactate levels > 2 mmol l^−1^; (4) to evaluate the ability of P(v–a)CO_2_/C(a–v)O_2_ to predict lactate clearance after hemodynamic optimization; (5) to evaluate the ability of P(v–a)CO_2_/C(a–v)O_2_ to predict VO_2_ changes after hemodynamic optimization; (6) to compare the number of patients with organ failure; and (7) to compare these effects on ICU length of stay, hospital length of stay, and 28-day mortality.

### Endpoints

The primary endpoint is the number of patients with a lactate clearance over 10% between H0 and H2.

The secondary endpoints are as follows: (1) blood lactate levels at H12, H24, and H48; (2) lactate clearance at H12, H24, and H48; (3) relationship between pCO_2_ gap and blood lactate levels at H2, H12, and H24; (4) relationship between p(v–a)CO_2_/C(a–v)O_2_ and lactate clearance at H2, H12, and H24; (5) relationship between P(v–a)CO_2_ /C(a–v)O_2_ and VO_2_ at H2, H12, and H24; (6) SOFA score on days 0, 1, 2, 7, and 28; and (7) ICU length of stay, hospital length of stay, and 28-day mortality. Patients' follow-up is 28 days after enrolment.

### Data Collection

Data are collected and recorded on eCRF by a physician who is not involved in the care of the patient, and who is blind to the study groups. All patient-related data are anonymously and numerically coded. Data collection encompasses the following: (1) the demographic characteristics of the population (age, sex, weight, SOFA score, SAPS II score, hospital and ICU admission reason, past medical history, and comorbidities), (2) the pharmacological treatment (type and infusion rate of sedation drugs, maximal dose and duration of norepinephrine and dobutamine, amount of fluid, fluid balance, and amount of blood transfusion), (3) the respiratory parameters (tidal volume, respiratory rate, positive end-expiratory pressure, inspiratory O_2_ fraction, end-tidal CO_2_, and plateau and peak pressure), (4) the hemodynamic state (heart rate, arterial blood pressure, pulse pressure, hourly urinary output, cardiac output, respiratory variation of pulse pressure, and/or stroke volume), and (5) the biological marker (hemoglobin, arterial and mixed venous oxygen saturation, partial pressure of CO_2_ in arterial and venous blood, blood lactate level, bicarbonate, base excess, creatinine, sodium, potassium, and chloride).

The study may be discontinued for an individual patient if the patient (or the person designated by the patient) so desires or if decided by the investigator. Every effort will be made to comply with the study protocol. However, the clinician in charge of the patient may deviate from these instructions at any time if he/she considers it necessary. He/she must note this decision and the reason for it in the case report form. If the study is discontinued, no provision is made for patient replacement. Likewise, patients who discontinued the study for whatever reason will receive standard care for the disease in question.

## Statistics

### Sample Size Calculation

Based on actual literature, lactate clearance over 10% over a 2-h period is between 50 and 60%. Assuming our hypothesis that an algorithm based on CO_2_-O_2_-derived indices can reach a 2-h lactate clearance over 80%, 82 patients should be randomized in each treatment group with a bilateral alpha risk of 5% and a power of 80%. After taking into account the risk of missing data and patients lost to follow-up (10% of incomplete data), we fixed the sample size to 180 patients, with 90 in each treatment arm.

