### Data Analysis Plan

Normality will be checked graphically with histograms and QQ plots and by the Shapiro-Wilk normality test. Continuous variables will be described as mean ± SD or as median (25–75%, IQR) as appropriate, and categorical variables will be described using a frequency table with a 95% confidence interval for the proportion. The data will be analyzed by intention to treat and per protocol. The two groups will be presented comparatively after randomization. Evaluation of the primary endpoint will be performed by Fisher's exact test. Categorical variables will be compared by Fisher's exact test. Continuous variables will be compared by Student's *t*-test or the Wilcoxon*-*Mann*-*Whitney test, as appropriate. Statistical analysis will be carried out using the R studio software. A *p*-value <0.05 will be considered statistically significant.

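### The stated 80% power fits an uncorrected chi-square test at 60% v 80%; Fisher's exact test, the named primary test, has about 75% at that design point after the planned 10% loss

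*Protocol article*

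**What the plan says.** The Sample Size Calculation section of the protocol article gives these elements:

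- Control arm: "lactate clearance over 10% over a 2-h period is between 50 and 60" percent.
- Algorithm arm: it "can reach a 2-h lactate clearance over 80" percent.
- Size and error rates: "82 patients should be randomized in each treatment group with a bilateral alpha risk of 5% and a power of 80" percent.
- After an allowance of 10% for incomplete data: "we fixed the sample size to 180 patients, with 90 in each treatment arm".

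The section names neither the test nor the formula behind the 82. The Data Analysis Plan section then states: "Evaluation of the primary endpoint will be performed by Fisher's exact test". The threshold is p < 0.05. Allocation is 1:1, stratified by centre and type of shock (Randomization section).

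**The concern.** A stated power is a property of a particular test at a particular design point. Fisher's exact test is conservative in a two-arm comparison of this size: its true type I error lies well below the nominal 5%, so it needs more patients than the uncorrected chi-square test for the same power. If 82 was derived for the chi-square test and the analysis uses Fisher's test, the 80% does not describe the planned analysis. At stake is the chance of missing the assumed effect on the sole primary endpoint. At the design point this is about 25% (100 − 75.3) and not the 20% that the article implies.

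**Working it through.** **Inputs.** Two-sided alpha 5%, power 80%, control rate 50–60%, algorithm rate 80%, 82 per arm before inflation, 10% incomplete data and 90 per arm after inflation (all from Sample Size Calculation); Fisher's exact test at p < 0.05 (Data Analysis Plan).

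**Step 1. Reproduce the 82.** The pooled chi-square formula without continuity correction, at 60% v 80% (mean rate 0.70, difference 0.20), gives

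n = [1.960·√(2·0.70·0.30) + 0.8416·√(0.60·0.40 + 0.80·0.20)]² / 0.20²
= [1.2702 + 0.5323]² / 0.04 = 81.2, so **82 per arm**.

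Alternatives at 60% v 80%:

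- Unpooled variance: (1.960 + 0.8416)²·0.40/0.04 = 78.5, so 79.
- Arcsine: 7.849 / [2·(1.1071 − 0.8861)²] = 80.3, so 81.
- Pooled with continuity correction: 90.9, so 91.

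With the pooled formula, control rates of 50% and 55% give 39 and 54 per arm (45 and 62 with continuity correction). The printed figure therefore points to 60% v 80% and the uncorrected pooled formula.

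**Step 2. Evaluable patients.** 90 × 0.90 = 81 per arm.

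**Step 3. Power of each test at 60% v 80%.** All pairs of binomial counts were enumerated, and the probability of those with two-sided p < 0.05 was summed.

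| Evaluable per arm | Fisher's exact | Chi-square, uncorrected |
|---|---|---|
| 81 | 75.3% | 80.2% |
| 82 | 75.9% | 80.7% |
| 89 | 79.6% | 83.7% |
| 90 | 80.2% | 84.2% |

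At 81 per arm the test alone accounts for 80.2 − 75.3 = 4.9 points. In a search upward from 80 per arm, Fisher's test first reaches 80% at 90 evaluable, which is the whole planned arm.

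**Step 4. True type I error.** At 81 per arm, with common rates of 60% to 80% in steps of 5 points, Fisher's size is 3.0–3.5% and that of the uncorrected chi-square test is 4.8–5.1%. The chi-square test can go slightly over 5%: at a 60% common rate its size is 5.2% with 90 per arm and 5.4% with 89.

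**Step 5. Sensitivity over the article's own range.** Fisher's exact test, 81 per arm:

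| Control v algorithm | Power |
|---|---|
| 60% v 80% | 75.3% |
| 59% v 80% | 79.3% |
| 58% v 80% | 82.9% |
| 55% v 80% | 91.1% |
| 50% v 80% | 97.7% |
| 60% v 81% | 80.0% |

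**Step 6. Stratified alternative.** The Cochran-Mantel-Haenszel test was simulated at 81 per arm and a homogeneous 60% v 80%, with eight strata (two centres by four shock types). The stratum sizes are assumed, since the article gives none. Power was about 80% without continuity correction and about 75% with it.

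**The case against.** The strongest reply is that 60% v 80% is the least favourable corner of the planning range. The article puts the control rate at 50–60% and the algorithm rate above 80%. Two points off the control rate, or one point on the algorithm rate, brings Fisher's power back to 80% or more. A reader might infer from the 75% that the trial is underpowered across its planning range; the article's own figures do not support that. The shortfall still stands at the point where it is claimed, because the 82 and its 80% power reproduce only at a 60% control rate.

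Second, a reader might take it as documented that the trial was sized for a chi-square test. It is not: no sizing test is named, and this is an inference from the arithmetic. The conclusion does not depend on it, since 82 per arm does not give Fisher's test 80% power at 60% v 80%, whichever formula produced it.

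Third, all 90 per arm analysed by intention to treat would give 80.2%. That holds only if every H0 and H2 lactate is known, and the article itself budgets for 10% incomplete data. It also lists exclusions (an ICU stay under 48 h, hemodynamic deterioration) and makes no provision for replacing patients who discontinue. Ninety evaluable is the best case.

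Fourth, Fisher's test is valid. Its conservatism costs power but does not inflate type I error or bias the estimate. This stands, and it limits how serious the point is.

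**Conclusion.** The point holds in a limited form. The 80% power and the named primary test do not belong together at the design point on which the 82 rests: Fisher's exact test gives 75.9% at 82 per arm and 75.3% at 81, a shortfall of 4 to 5 points. Choosing Fisher's test uses up the whole 10% allowance, because 80.2% is reached only with 90 evaluable per arm. The result assumes a true 60% v 80%, two-sided 5%, and 81 evaluable per arm; at lower control rates the shortfall disappears.

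This should be fixed, but it is not a critical flaw: the test is valid and the remedy is a matter of wording.

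A minor note concerns the loss allowance. 82/0.90 = 91.1 would round up to 92 per arm, while 82 × 1.10 = 90.2 is close to the 90 chosen. The resulting 81 instead of 82 evaluable costs about 0.6 points under Fisher's test and 0.5 under chi-square, and chi-square power stays at 80.2%. It carries no weight of its own.

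**What to change.** Before any unblinded analysis, do one of the following:

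1. Name as the primary test the chi-square test without continuity correction. Power at 60% v 80% with 81 per arm is then 80.2%. The price is a type I error that sits close to 5% and can slightly exceed it (Step 4).
2. Name a Cochran-Mantel-Haenszel test stratified by centre and type of shock, and state that it is run without continuity correction. This matches the stratified randomisation. With the correction, it would regain essentially nothing over Fisher's test.
3. Keep Fisher's exact test and restate the power as about 75% at 60% v 80% with 81 evaluable per arm, adding that it is about 91% at a 55% control rate and 98% at 50%.

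Whichever is chosen, the sample size section should name the sizing test and the 60% control rate, and give 81 as the evaluable number per arm. The cost is a sentence or two, or a less favourable stated power; no extra patients are needed. If outcomes by arm have already been seen, only the third option remains, since changing the primary test then would look data-driven.

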### Data Analysis Plan

Normality will be checked graphically with histograms and QQ plots and by the Shapiro-Wilk normality test. Continuous variables will be described as mean ± SD or as median (25–75%, IQR) as appropriate, and categorical variables will be described using a frequency table with a 95% confidence interval for the proportion. The data will be analyzed by intention to treat and per protocol. The two groups will be presented comparatively after randomization. Evaluation of the primary endpoint will be performed by Fisher's exact test. Categorical variables will be compared by Fisher's exact test. Continuous variables will be compared by Student's *t*-test or the Wilcoxon*-*Mann*-*Whitney test, as appropriate. Statistical analysis will be carried out using the R studio software. A *p*-value <0.05 will be considered statistically significant.

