## Materials and Methods

### Study Design

LACTEL (*Traitement de l'hyperLACtaTEmie du patient en insuffisance circuLatoire aigue basée sur l'analyse des indices dérivés du CO2: étude randomisée prospective de supériorité*) is a randomized, prospective, multicentric, single-blind, parallel-group, superiority study. It compares the treatment of hyperlactatemia using an algorithm based on the pCO_2_ gap and the pCO_2_ gap/P(a-v)O_2_ ratio vs. usual clinical practice in patients with shock. The study was approved by an independent ethics committee (*Comité de Protection des Personnes Sud Ouest et Outre-Mer* on 8 July 2021, 2021-A101451-40) and was registered (ClinicalTrials.gov: NCT05032521). The study is conducted in ICUs of the University-affiliated tertiary Hospital of Dijon and the University-affiliated tertiary Hospital of Besancon, France. All the patients or their next of kin received written information about the study and gave consent to participate. The design of the study respects the requirements of the Medical Research Involving Human Subjects Act and the Declaration of Helsinki.

Standard protocol items: the study follows the SPIRIT Recommendations for Interventional Trials, and the SPIRIT protocol chronology is presented in Table 1.

**Table 1 T1:** Protocol timeline.

	**ICU admission**	**Enrolment**	**Follow-up**				**End of study**
	**H0 (Day 0)**	**H0 (Day 0)**	**H2**	**H12 (Day 0)**	**H24 (Day 1)**	**H48 (Day 2)**	**Day 28**
Enrolment validation	X						
Randomization		X					
Clinical examination	X	X	X	X	X	X	X
Standard analysis set	X	X	X	X	X	X	
Study analysis set	X	X	X	X	X	X	
Clinical and biological data		X	X	X	X	X	X
Hemodynamic monitoring		X	X	X	X	X	
SOFA score		X	X	X	X	X	X

*ICU, intensive care unit; H, hours at or after enrollment; D, day*.

The first patient was included in December 2021, and the last follow-up was planned until October 2024.

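### Randomisation is stratified by centre and type of shock, but the yes/no endpoints are tested unstratified, which loses power to the extent that those factors predict 2-hour lactate clearance

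*Protocol article*

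**What the plan says.** The Randomization section of the protocol article states: "The 1:1 ratio randomization (stratified on center and type of shock) is performed by the investigator". Two hospitals take part (Study Design). Four types of shock are listed under Study Population, though the article does not say that these four are the stratification levels.

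The Data Analysis Plan fixes the tests. For the primary endpoint: "Evaluation of the primary endpoint will be performed by Fisher's exact test". For the rest: "Categorical variables will be compared by Fisher's exact test". The second sentence covers the count of patients with lactate below 2 mmol/l and 28-day mortality. No stratified test, adjusted model or other use of the two factors appears in the article.

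The Sample Size Calculation concludes that "82 patients should be randomized in each treatment group with a bilateral alpha risk of 5% and a power of 80"%. It assumes a control response of 50 to 60% and an algorithm response of 80%. The total is then raised to 180, 90 per arm, for 10% incomplete data.

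**The concern.** Stratified allocation balances the arms on the chosen factors, so differences between strata no longer contribute to the chance difference between arms. A single collapsed 2x2 table still counts those differences as error. If the factors predict the outcome, the p-value is on average too large, the real type I error is below the nominal 5%, and a true effect is more easily missed. The balance obtained at randomisation would then not be used in the analysis that decides superiority.

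The article names the deciding test, so this is a choice it has fixed rather than a detail left to an unseen analysis plan.

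**Working it through.** **1. The plan's own figure.** Inputs from the Sample Size Calculation: control 60% (the end of the range that reproduces 82), algorithm 80%, two-sided 5%, power 80%. The pooled two-proportion formula without continuity correction is

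n = [z(0.975)·√(2·p̄·q̄) + z(0.80)·√(p1·q1 + p2·q2)]² / (p2 − p1)²

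With p̄ = 0.70: [1.960·√0.42 + 0.842·√0.40]² / 0.20² = (1.270 + 0.532)² / 0.04 ≈ 81.2, so 82 per arm. The stated figure reproduces. A control rate of 55% would give 54 and 50% would give 39.

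**2. The named test at that size, strata ignored.** Full enumeration of the 2x2 tables at 60% v 80%:

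| Per arm | Fisher power | Uncorrected chi-square power | Loss |
|---|---|---|---|
| 81 (90 less 10%) | 75.3% | 80.2% | 4.9 |
| 82 | 75.9% | 80.7% | 4.8 |
| 90 | 80.2% | 84.2% | 4.0 |

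At 82 per arm and 60% in both arms, true size is 3.3% for Fisher and 4.8% for chi-square. This gap is Fisher's own conservatism and would exist under any randomisation scheme.

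**3. Why the strata matter: an illustration.** Assume half the patients are in strata with a 40% response and half in strata with 80%, the same in both arms. The overall rate is 60%. The collapsed table uses variance 0.60·0.40 = 0.24 per patient. With balanced strata the true variance is the within-stratum average, (0.24 + 0.16)/2 = 0.20. The nominal cut-off of 1.960 therefore acts as 1.960·√(0.24/0.20) = 2.147, and the real two-sided error is about 3.2%. With no difference between strata the two variances are equal and nothing is lost.

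**4. Size of the stratification effect alone.** Simulation: 100,000 runs, 82 per arm, overall 60% v 80%, common odds ratio. All of the following are assumptions, since the article gives none of them: 8 strata (2 centres by 4 shock types) exactly balanced by arm, centres 65/35, shock mix 45/18/12/25%, and the spread of control rates. CMH is the Cochran-Mantel-Haenszel test without continuity correction.

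| Control rates across strata | Power: Fisher | Power: chi-square | Power: CMH | CMH minus chi-square | Type I error: Fisher / chi-square / CMH |
|---|---|---|---|---|---|
| 60% in all | 75.8% | 80.7% | 80.7% | 0.0 | 3.2 / 4.7 / 4.8% |
| 53–71% | 76.2% | 80.9% | 81.2% | 0.3 | 3.2 / 4.7 / 4.9% |
| 47–80% | 76.1% | 81.0% | 82.1% | 1.1 | 2.9 / 4.2 / 5.1% |
| 41–87% | 77.1% | 81.9% | 84.2% | 2.3 | 2.3 / 3.5 / 5.0% |
| 36–92% | 77.8% | 82.7% | 86.3% | 3.6 | 1.9 / 2.9 / 4.9% |
| 27–97% | 78.8% | 83.9% | 89.7% | 5.8 | 1.1 / 1.8 / 4.9% |

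A separate simulation at 81 per arm gave, for chi-square v CMH, 80.4% v 80.4% (no spread), 80.6% v 81.4% (46–73%), 81.6% v 84.4% (34–83%) and 82.9% v 87.9% (24–91%).

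**5. The form of the stratified test.** With the continuity correction left on, CMH power in the first, third and fifth rows of the table falls to 75.5%, 77.0% and 81.7%, a loss of about 5 points. An exact CMH test also gives much back. In a smaller simulation (4,000 runs, 81 per arm, control rates 40–86%) it reached 80.8%, against 82.9% for uncorrected CMH and 81.0% for the unstratified chi-square test.

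**The case against.** The strongest reply is that no loss from ignoring the strata has been shown. The article gives no response rate by centre or shock type, and with no spread the loss is zero. The layout, the shock mix and the spreads are the analyst's own, and gains above about 2 points need control rates that differ by more than 40 points between strata. Fisher's test is valid: it errs on the safe side, and at 90 per arm with complete data its power is 80.2%, so the target is met before attrition. This all stands. It limits the point to one of efficiency.

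Two stronger readings are tempting. A reader might infer that the p-values are certainly too large because the strata are ignored. The documents support this only on condition that the factors are prognostic. The condition is plausible, because the sponsor chose these factors and the article argues that hyperlactatemia has different causes, but it is not quantified. A reader might also credit the whole gap between Fisher and CMH to stratification. Of the 8.5 points at 36–92% (77.8% v 86.3%), 4.9 separate Fisher from chi-square and 3.6 come from using the strata.

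The reply does not give a reason to keep the unstratified test. When the strata carry no information, CMH costs nothing against chi-square and still exceeds Fisher.

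**Conclusion.** The mismatch is plain in the text: allocation is stratified on two factors and the analysis uses neither. Its effect is in the conservative direction. It does not bias the estimated difference, and nothing in the article supports a claim of inflated false positives.

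At 60% v 80% and about 82 per arm, ignoring the strata costs 0 points of power if they are not prognostic, about 1 point with mild spread, and about 3 to 5 points with wide spread (nearly 6 in the most extreme setting tried). These figures rest on the assumed layout and spreads above. The separate cost of Fisher's conservatism, 4 to 5 points, needs no assumption about strata. It leaves about 76% power at the stated 82 per arm, where the formula used promises 80%. One change to the named test deals with both.

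**What to change.** In the Data Analysis Plan, replace the sentence on the primary endpoint so that it names one test in advance: a Cochran-Mantel-Haenszel test without continuity correction, stratified by centre and type of shock as entered at randomisation (in R, mantelhaen.test with correct = FALSE). Report the stratified risk difference with its 95% CI. Do not allow a switch to an exact form if strata turn out sparse: that would leave the primary test to be chosen after the data are seen, and would return much of the gain. With up to 8 strata in 162 to 180 patients (about 20 to 22 per stratum on average) some strata will be small, and the CMH test tolerates this.

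Use the same stratified method for lactate below 2 mmol/l and for 28-day mortality. Keep Fisher's exact test as a sensitivity analysis. If a separate analysis plan already specifies a stratified test, reconcile the two documents.

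The cost is a sentence or two, written before database lock. It needs no new data, no extra patients and no change to the sample size: with non-prognostic strata, uncorrected CMH has 80.7% power at 82 per arm, in line with the plan's own calculation.

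### 28-day mortality falls to an unadjusted Fisher's exact test, which is valid but inefficient: it uses neither the randomisation strata nor the baseline severity already collected

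*Protocol article*

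**What the plan says.** The Protocol article, Data Analysis Plan, fixes the same test twice: "Evaluation of the primary endpoint will be performed by Fisher's exact test", and "Categorical variables will be compared by Fisher's exact test". It adds: "The data will be analyzed by intention to treat and per protocol". It names no stratified or covariate-adjusted model. The only interval it mentions is a 95% confidence interval for a proportion, in the description of categorical variables.

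Mortality is not named in that section. It appears in Endpoints as part of the seventh secondary endpoint, "ICU length of stay, hospital length of stay, and 28-day mortality", and in Objectives as a comparison between the two strategies. It is a yes/no outcome, so the rule for categorical variables applies to it.

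The Randomization section allocates 1:1, "stratified on center and type of shock". Study Design names two hospitals, and Study Population lists four types of shock (septic, cardiogenic, hemorrhagic, post-operative). Data Collection includes "age, sex, weight, SOFA score, SAPS II score" and blood lactate. Table 1 schedules SOFA at enrolment, and H0 lactate must exist because the primary endpoint is measured from it.

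**The concern.** The design balances the arms within centre and type of shock, and the stated test then discards that information. It also leaves unused the baseline measures most likely to predict death. The Discussion itself treats the link of hyperlactatemia with shock severity and mortality as established, and it justifies the 2-hour lactate endpoint by an association with mortality. Readers will therefore look at the mortality result, although the trial was not sized for it.

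Two separate losses are at stake. Fisher's test spends less than the nominal 5%, which costs power whatever the covariates do. Ignoring strata and severity costs further power and precision, by an amount that depends on how prognostic they are. A p-value alone also says little about an unpowered outcome; an estimate with its interval would say more.

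**Working it through.** **Inputs from the Protocol article.** 90 per arm, two-sided 5%, two centres, four shock types, Fisher's exact test. It gives no mortality rate, mortality effect or prognostic strength, so those below are assumptions.

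**1. The plan's own figure.** The article sizes the primary endpoint only. With 60% v 80%, 80% power and the uncorrected normal approximation:

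n = [1.96·√(2·0.7·0.3) + 0.8416·√(0.6·0.4 + 0.8·0.2)]² / 0.2² = (1.270 + 0.532)² / 0.04 ≈ 81.2, so 82 per arm.

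The stated 82 is reproduced. There is no corresponding figure for mortality.

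**2. Actual size at 90 per arm.** For each pair of death counts, take whether the test rejects, weight by the two binomial probabilities, and sum:

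| Mortality in both arms (assumed) | Fisher | Uncorrected chi-square |
|---|---|---|
| 20% | 3.25% | 4.88% |
| 30% | 3.44% | 4.97% |
| 40% | 3.68% | 5.21% |
| 50% | 3.10% | 4.45% |

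Fisher's test leaves 1.3 to 1.9 of the 5 percentage points unused. This step needs no assumption about covariates.

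**3. Power, split into the two sources.** Fisher and chi-square are exact. The adjusted analysis is the standardised risk difference from logistic regression, simulated with 2 centres × 4 shock types, blocks of 4 and 1500 trials per scenario.

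| Assumed covariates | Assumed rates | Fisher | Chi-square | Adjusted | From dropping Fisher | From adjustment |
|---|---|---|---|---|---|---|
| Weak | 37.4% v 23.7% | 45.5% | 51.6% | 54.7% | 6.1 | 3.1 |
| Moderate | 36.5% v 22.4% | 48.7% | 54.9% | 60.8% | 6.2 | 5.9 |
| Strong | 36.7% v 21.8% | 53.7% | 59.8% | 71.7% | 6.1 | 11.9 |

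Simulation error is about √(0.25/1500) = 1.3 points.

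A second stratified simulation moved from Fisher to adjusted as 45% to 52%, 51% to 63% and 56% to 71%, gains of 7, 12 and 15 points. Taking off 6 for Fisher's conservatism leaves 1, 6 and 9. Setting its 71% against the exact 59.8% gives 11.2. So adjustment adds roughly 1–3, 6 and 11–12 points, and the last could be as low as 9.

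**4. Precision.** The ratio of adjusted to unadjusted standard error of the risk difference was 0.977, 0.935 and 0.881 in the first simulation and 0.99, 0.94 and 0.89 in the second. The reductions are about 1–2%, 6–7% and 11–12%. For the weak scenario the unadjusted 95% half-width would be 1.96·√(0.374·0.626/90 + 0.237·0.763/90) = 13.3 points; times 0.977 it is 13.0. The same sum gives 13.2 to 12.3 (moderate) and 13.1 to 11.6 (strong).

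**5. Other assumptions.** With one severity score of AUC 0.63, 0.72 or 0.79 and mortality of 40% v 20%, power is 80% with Fisher, 84% with chi-square, and 84%, 89% or 92% with adjusted logistic regression. With equal mortality of 30–50%, the adjusted logistic test had a simulated size of 4.5–5.5% and the standardised risk difference 4.9–5.8%.

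**6. A modest effect.** For 40% v 30%, power is 24% with Fisher and 29% with chi-square.

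**The case against.** The strongest reply is that nothing here is an error. An unadjusted Fisher's test after stratified randomisation keeps the type I error at or below 5%. A reader might infer from the mismatch with the strata that the test is invalid; step 2 shows the opposite, and that part of the objection stands in full.

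A reader might also infer that the reported mortality interval will be too wide. The article specifies no between-arm interval, so there is none to criticise. The half-widths in step 4 only show what adjustment would be worth if one were reported.

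Nor should the whole gain be credited to adjustment. About 6 points come from leaving Fisher's test, which is most of the gain with weak covariates and about half with moderate ones. The strata's share was not separated from that of SOFA, age and lactate.

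It can be said that adjusted models belong in a statistical analysis plan that is not shown. One may exist there, so it cannot be claimed that Fisher's test is the trial's only mortality comparison; it is the only one this article states. But the Fisher rule is stated text and can be assessed as such.

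Finally, mortality is secondary and unpowered, and the same test is fixed for the primary endpoint, where it matters more: exact power for 60% v 80% at 90 per arm is 80.2% with Fisher against 84.2% with chi-square. That lowers the weight of the mortality point but does not remove it.

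**Conclusion.** The point holds as lost efficiency, with no inflation of error. By type, 28-day mortality goes to an unadjusted Fisher's test that ignores the strata and available baseline severity, and the article states no between-arm effect estimate for it.

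The firm part is Fisher's conservatism: a size of about 3.1–3.7%, which depends only on mortality lying between 20% and 50%, and about 6 power points at the rates examined. The adjustment gain is conditional. It is negligible to small if the covariates are weak and substantial only if they are strong, and the article gives no figure to choose between these. The precision gain applies to the standardised risk difference; logistic adjustment does not shrink the standard error of the log odds ratio.

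The power figures assume a fall of 14–15 points in mortality, which the article does not claim. The comparison will remain inconclusive for modest effects under any analysis considered here. This is a cheap improvement that should be made; it does not threaten the trial's validity.

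**What to change.** For 28-day mortality, prespecify a logistic regression with treatment, centre, type of shock, SOFA at enrolment, age and H0 lactate. Report the standardised (marginal) risk difference with a 95% CI, name the variance estimator, and keep Fisher's test as a sensitivity analysis.

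Use only covariates measured before randomisation. The timing of SAPS II is not stated, so include it only if it is scored from pre-randomisation data. Prespecify, without reference to outcome by arm, how sparse shock types will be collapsed.

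The cost is a short addition to the analysis plan, with no new patients or data. The downside is model size: treatment 1, centre 1, type of shock 3, SOFA 1, age 1 and lactate 1 make 8 parameters plus an intercept. At the rates assumed above, deaths would number about 90 × (0.374 + 0.237) = 55, within an assumed 50–60, so the covariate list should not grow further.
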